### Interventions

The experimental, theoretically underpinned RECALL programme and the active control interventions both incorporate group and whole-class activities designed to be fun for young children. The programmes are comparable in their structure, format and dosage (intervention frequency and duration). They both consist of six, 40-min sessions that are repeated three times per week for 6 weeks (18 sessions in total). The first session each week will be delivered by the health professionals who will model the activities for the teachers so that they can deliver the two further practice sessions.

#### Experimental intervention: RECALL

RECALL is a theoretically underpinned, multi-component, manualised intervention that explicitly targets WM skills in 4–5 year olds to enhance attention and language skills. It is underpinned by individual change theory (why the intervention components are expected to benefit WM and produce near- and far-transfer effects) and systems theory (considering the role of the school context in affecting change) [52–55]. It was co-produced through a series of workshops with one group of teachers, parents and health professionals in an inter-sectoral partnership [54].

##### Individual theory of change

The tasks included in RECALL are based on evidence from a recent systematic review [56]. The review found certain tasks designed to either target WM directly (listening recall and odd-one-out) or indirectly (cognitively-demanding physical activity, inhibition, phoneme awareness and fantastical play) produced improvements on WM and some benefits for near-transfer activities [57–67]. The common ingredient across the effective interventions was predominantly the executive-loaded nature of the trained task, i.e. training on a task that taps into attentional and processing resources under executive control and not just the storage of information [56]. It has been suggested that repeated practice on executive-loaded working memory (ELWM) tasks (rather than practising storage-only, short-term memory tasks) may improve the efficiency of processing or perhaps even facilitate the storage of information in WM [58, 68]. Based on this evidence, all of the components in RECALL are executive-loaded tasks, where attention must be divided between the storage and processing demands of the task. This may overlap with the way attention is used in everyday (real-world) activities. Hence, since treatment effects are more likely to transfer from trained activities to activities with overlapping features [26], the direct training on ELWM tasks in RECALL may benefit untrained WM tasks and real-world skills including attention and language.

In addition to directly training ELWM skills, RECALL includes two other tasks that were identified in the systematic review as having potential. Interventions targeting phoneme awareness skills [64, 65] and fantastical play [66] were found to impact WM indirectly. These are included in RECALL due to their associations with functional language outcomes and attention. They are complementary to and consistent with the theory that ELWM tasks support WM because they are also executive-loaded tasks, i.e. they tap into processing and attentional resources under executive control. Phoneme awareness is the ability to isolate and manipulate sounds in spoken words [69]. Improving phoneme awareness might enhance the phonological mechanisms underlying WM, through increasing the efficiency of processing and supporting the creation of accurate, structured phonological representations. This may in turn support language development since our ability to recall words depends on their phonological representations in long-term memory [70, 71].

Fantastical play is a type of pretend play that is fantasy-oriented [66]. For example, pretend play could involve pretending to make tea, whereas fantastical play might involve pretending to make swamp tea for a giant. Engaging in fantastical play may support children’s WM and other executive functions which are used to support switching between fantasy and reality and remembering the rules/scripts of the pretence [72, 73].

##### Systems theory of change (intervention delivery model)

The theory underpinning how the ELWM tasks in RECALL can be delivered in the classroom was developed through the co-production workshops. The socio-ecological model [74] was used as a framework to inform the development of an intervention logic model (i.e. a pictorial representation of the relationships between the required resources, activities needed, mechanisms of change and desired outcomes [33]). This supported the identification of multi-level factors that may impact on the programme delivery in the classroom, e.g. the timing of intervention sessions in the classroom, the availability of resources and staff training needs. Consequently, the theory underpinning the delivery of RECALL is that the co-designed tasks will work in the classroom context when staff are supported with adequate training and a detailed manual. The health professionals model one RECALL session per week in the classroom. The teachers follow the activity plan in the RECALL manual so that they become familiar with the tasks and can deliver them independently a further two times in the week. Detailed session plans and accompanying materials such as picture stimuli and worksheets are provided in the RECALL manual.

##### RECALL components

The ELWM tasks incorporated into RECALL include direct training on two ELWM tasks (listening recall and odd one out [58]), phoneme awareness training [64, 65] and fantastical play [66]. Table 2 provides a description of each task.

**Table 2 Tab2:** RECALL components and task progression

RECALL component (ELWM task)	Task progression
Listening recall (direct WM training)	
- This task targets verbal ELWM. - The children listen to a short sentence, judge whether it is true or false and recall the last word of the sentence.	The number of to-be-remembered words increases from one word in week one to two words by week 6.
Odd one out (direct WM training)	
- This task targets visuospatial ELWM. - The children look at three pictures in a grid, decide where one the odd one out is (left, middle or right), then recall the location of the odd one out picture.	The number of to-be-remembered locations increases from one in week one, to three or four by week 6.
Phoneme awareness training	
There are four types of phoneme awareness task in RECALL, focusing on developing awareness of the initial sounds in words. 1. Alliterative matching: finding things that start with a target sound. E.g., “Book starts with ‘b’. Can you find the other things that start with ‘b’?” 2. Segmenting initial sounds: “what sound does ____ start with?” 3. Alliterative matching and blending the target to generate new words: “Find the one that starts with ___? Let us think of other things that start with _” 4. Blending sounds to identify words: “Look at these pictures. Can you find the b – all?”	The four tasks develop from the easiest (alliterative matching) to the most difficult (blending sounds) [75]. The difficulty level of the practice items in each task progresses from early to late developing phonemes based on typical speech sound development [76].
Fantastical play	
There is no direct training on fantastical play in RECALL. This is integrated into the programme through the use of a fantastical theme for each session, e.g. superheroes. However, the direct ELWM and phoneme awareness tasks incorporate the theme of each session throughout i.e., the words and pictures used relate to the theme.	

##### Task progression

The manipulation of WM loads on a trial-by-trial basis may be important for improving WM where research has particularly shown the value of adaptive training, i.e. task difficulty that increases or decreases automatically based on an individual child’s performance [77]. As RECALL is to be delivered in the group context, individual adaptive profiles cannot be rolled out. Instead, the programme is designed to become progressively more difficult across its 6 weeks. Table 2 shows how the direct ELWM and phoneme awareness tasks in RECALL progress in difficulty across the course of the 6-week programme. Due to two novel features of the RECALL trial (the age of the children and the group nature of the intervention), establishing the span level at which to commence training and how to increase the level of difficulty from week to week was reasoned from previous studies with older children [58]. The appropriateness of this for 4–5 year olds will be explored in this feasibility trial.

##### Dosage

The amount and intensity of training is often poorly reported in WM studies [56].^2^ The dosage to be implemented in RECALL is based on the best available evidence from the systematic review which indicated that 11 trials (practice items) of each direct ELWM task (listening recall and odd one out) delivered three times per week for 6 weeks was effective [58]. For the phoneme awareness tasks, the dose (number of trials) administered in previous interventions is unclear. However, several studies identified that training sessions lasted 10–15 min [64, 65] and this is replicated in RECALL.

##### Structure of RECALL sessions

Each of the six RECALL sessions follows the same format, incorporating whole-class and group activities (Fig. 3). The fantastical theme for the week is introduced using a puppet who tells the children they are going on an adventure. The children are encouraged to enter into the fantasy by moving like characters in the fantastical land, e.g. posing like a superhero. The children are then divided into three groups that rotate around the direct ELWM and phoneme awareness training activities. The sessions close with another whole-class activity so the puppet takes them back to the reality of the classroom.

**Fig. 3 Fig3:**
[figure not shown]
Structure of RECALL session

#### Active control group: existing ALP

The active control group in this study will receive an existing intervention (ALP) developed and used by the RISE teams. This has been selected as the active control condition because the programme is delivered in the same way as RECALL, i.e. the health professionals model the activities for the teachers and provide them with session plans so that they can replicate them. The programme also has the same dosage as RECALL (six, 40-min sessions that are repeated three times per week delivered once by the health professionals and twice the teachers). This recognises the importance of equating the training intensity between groups in WM research [24, 79].

The crucial difference between this programme and the experimental RECALL intervention is that the ALP intervention is not underpinned by WM theory. It aims to improve children’s attention and listening skills through repeated practice at listening tasks (e.g. the facilitator reads a story and the children must shake a musical instrument when they hear a particular word). It focuses on teaching children the importance of listening and on the use of visual, verbal and behavioural strategies to support listening, e.g. proximal praise. The tasks do not require the children to recall verbal or visuospatial information and they are not all executive-loaded. Whether this intervention is sufficiently different to act as a comparator in a full CRT will be explored in this trial.

#### No intervention control: education as usual

The two schools in this arm of the trial will not receive any whole-class interventions such as RECALL and the active control intervention during the 6-week trial period. Their teachers will be delivering the education curriculum as usual. How the teachers in these classes support the children’s attention and language skills during the study period will be explored in semi-structured interviews at the end of the trial.

### Compliance and fidelity

To enhance the implementation of RECALL, the health professionals, who will be modelling the programme each week for the teachers, will attend a 2-day training course prior to delivering it. They will be given the detailed programme manual which they will also supply to the teachers. To monitor compliance with the programme delivery and dosage, the health professionals and teachers will be asked to keep a simple log of their implementation (e.g. how often they delivered the programme and how long for). To monitor fidelity, three RECALL sessions in each school (one delivered by the health professional team and two by the teacher) will be observed by the first author. One of the health professional sessions and one of the teacher-delivered sessions will be observed simultaneously by a second member of the research team who will independently rate the delivery. Agreement between the raters will be checked by a third member of the team.

The researchers will use a structured observation tool designed within Carroll et al.’s (2007) [80] conceptual framework to explore four key elements of implementation (content, coverage, frequency, duration) and four moderating variables (intervention complexity, facilitation strategies, quality of delivery and participant responsiveness). Since this is a feasibility study, some adaptation to the intervention will be allowed (i.e. the researchers may address any problems raised by the health professionals or teachers). Any advice given will be recorded and examined in the process evaluation [81]. The interventions will be discontinued if a teacher withdraws from the study. If a health professional withdraws, another member of staff will be recruited and trained.

### Blinding

The school participants (principal, teachers and classroom assistants) and parents/guardians in the two intervention groups will be blinded to their group allocation. It is especially important that teachers and parents are blinded to group allocation, as their ratings of children’s attention skills will be used as outcome measures [25]. Maintaining the teachers’ blinding for the duration of the trial may be challenging, especially if the participating schools are in close geographical proximity to each other. This will be explored as part of the process evaluation in this study. Blinding of the health professionals to the schools’ allocation will not be possible as the teams will inevitably know which intervention they are delivering. The risk of this influencing the outcomes will be minimised further by the blinding of the research assistant (RA) who will be collecting the outcomes data. Whether the RA becomes aware of group allocation will also be investigated during the process evaluation.

### Outcome measures

Table 3 details the data that will be gathered at the cluster and individual levels to meet the primary objectives of this study regarding the acceptability of RECALL in the school setting and the feasibility of the trial processes.

**Table 3 Tab3:** Acceptability and feasibility data at the cluster and individual levels

Data	Cluster level	Individual level
Acceptability of RECALL intervention and its manual to health professionals and teachers	Measures of compliance and fidelity.	Qualitative data: • Semi-structured interviews • Comments on intervention logs • Feedback from pre-study training provided for health professionals.
Compliance	Number of sessions delivered in each cluster	Qualitative data from semi-structured interviews including reasons for any sessions not being completed.
Fidelity	Structured observations by research team following Carroll et al. (2007) Research team records of any advice given.	–
Recruitment, consent and sampling procedures	Number and proportion of schools: • Meeting eligibility criteria • Approached • Principals who consent • Teachers who consent Number and proportion of children identified by teachers in each of the 3 sub-groups.	Number and proportion of parents who consent
Attendance levels and loss to follow-up.	Number of completed interventions	Number of standardised assessments, teacher rating scales and parent rating scales completed post-intervention
Acceptability of randomisation	School consent rates and reasons given for participation/non-participation.	Qualitative data: teachers’ perspectives on random allocation.
Acceptability of active control intervention as a comparator to RECALL	–	Qualitative data: health professionals’ perspectives on similarities/differences between the programmes. Observations of delivery by research team.
Exploration of education as usual	–	Qualitative data–semi-structured interviews with teachers in the education as usual control arm.
Acceptability of outcome measures for the children, teachers and RISE teams	–	Number of completed assessments for each child at each time point Number lost to follow-up and reasons why if possible Quality of audio-data will be reviewed Qualitative data: semi-structured interviews
Unexpected adverse effects	Any unanticipated effects will be recorded by the RISE team and teachers	
Blinding	Qualitative data: recording if blinding maintained at end of study.	

### Data collection

The acceptability and feasibility data will be gathered throughout the study and during the process evaluation (see Fig. 1). In WM research, it is essential to demonstrate clear causal pathways [25]. A future large-scale trial of the effectiveness of RECALL would therefore have to include a range of measures of children’s outcomes including measures of the trained activities (WM and phoneme awareness skills), untrained WM tasks (near-transfer) and attention and language skills (far-transfer effects). Testing the feasibility and acceptability of measuring all of these skills with 4–5 year olds, for whom the range of standardised assessments is limited, is one of the key objectives of this feasibility trial. This will occur at two points, baseline and post-intervention (see Fig. 2). Four types of measurement will be trialled with the sample of ten children in each cluster.Standardised assessments administered directly with the children by a trained research assistant (RA).The RA, who will be blinded to group allocation, will withdraw children individually from their classroom for approximately one hour at each time point to complete the following standardised assessments:Phoneme awareness: The Preschool and Primary Inventory of Phonological Awareness (PIPA) [82]. This test is standardised for children aged 3 years to 6 years 11 months. It includes six subtests examining a range of phonological awareness skills. The phoneme isolation subtest will be used to directly assess children’s ability to identify the initial sound in a word, thereby providing a measure of a task directly trained in RECALL.Working memory: The Automated Working Memory Assessment (AWMA) [83] is a computerised assessment that will be administered using a laptop. This test has good validity as a measure of WM compared to other assessments [84]. Good test-retest reliability has also been demonstrated [15] and this measure is used widely in WM research. Two subtests will measure trained executive-loaded WM skills (listening recall and odd one out). Four further subtests will measure WM tasks not directly trained in the intervention (near-transfer effects). These subtests (digit recall, block recall, counting recall and non-word recall) have been selected due to their use in previous studies [58, 85].Attention: NEPSY-II–A Developmental Neuropsychological Assessment (NEPSY) [86]. Standardised, performance-based measures of attention for children under 6 years are limited [87]. The NEPSY-II is one of the few available assessments that includes attention subtests suitable for children of 4–5 years and (or its previous edition) has been administered in relevant studies [67].2.Language: The New Reynell Developmental Language Scales (NRDLS) [88] is a standardised assessment for children aged between 3 years and 7 years 6 months. It has two scales: one that examines children’s understanding of selected vocabulary items and grammatical features (the Comprehension Scale); and another that tests children’s production of the same features of language (the Production Scale). This test is widely used in clinical and research contexts [89] in the identification of language impairment. It uses objects (rather than picture stimuli) during the assessment and this should make it accessible to the target population in this study.3.*A teacher rating scale of the child’s attention in the classroom:* The Behaviour Rating Scale of Executive Function-Preschool Version (BRIEF-P) [90]. This tool is designed to specifically measure the behavioural characteristics associated with executive function skills including WM. It is a standardised, validated scale consisting of 63 items that can be used with children from 2 years to 5 years 11 months. It has good clinical utility and sensitivity and has been shown to complement performance-based measures of executive functions including WM [91, 92].4.*A parent rating scale of the child*’*s language and communication skills at home.* The Focus on Communication Outcomes Under Six (FOCUS) [93]. This has shown excellent test-retest reliability and internal consistency [94]. The forms will be posted to the parents one week before each data collection point and they will be asked to return the form to their child’s teacher. The completed forms will be collected by the RA along with the teacher-completed BRIEF-P.5.*Weekly monitoring of the child’s performance on the trained tasks.* Capturing individual responses will be an important part of a large-scale CRT due to the need for WM training to be adaptive. Therefore, assessing the feasibility of measuring children’s progress from week to week is an important part of the current feasibility study. For the classes receiving RECALL, the children’s performance on the direct WM and phoneme awareness tasks will take place during the first session each week which is delivered by the RISE NI teams. It is anticipated that the presence of additional adults in the classroom will facilitate this process. Each child will have a RECALL booklet in which they will complete the tasks using stampers or by drawing circles around the target pictures to indicate their responses. This will not be possible for some tasks that require purely verbal responses. For these tasks, digital voice recorders will be used (with parental consent) to record what the children say. There are significant uncertainties around the feasibility of audio-recording such data amidst the background classroom noise. Due to the level of uncertainty around this method, we aim to carry this out with just five, randomly selected children, in one of the RECALL classes. The voice recorder will be placed in a small gadget-holder which the children will wear across their bodies. A tie-clip microphone, connected to the recorder, will be placed on the children’s jumpers or lapels. The devices will be switched on and off by the teacher or classroom assistant.

### Data analysis

The feasibility data will be analysed and reported descriptively using means, frequencies and percentages. The data will be summarised and presented graphically. A CONSORT flow diagram will be used to report the response, recruitment and retention rate of clusters and individual participants at each point of the study. Where available, reasons for attrition and loss to follow-up will be reported.

Regarding the data obtained from the outcome measures completed with the children, statistical significance of treatment effects will not be analysed as this study would be under-powered for this purpose. However, between group comparisons will be conducted to inform the statistical model for the future trial. This will include two elements: (1) a series of one-way analyses (ANOVAs) of the baseline data of children’s standardised scores on the working memory (AWMA), attention (NEPSY subtests) and language measures (CELF-P) to investigate pre-intervention group differences; and (2) a series of analyses of covariance (ANCOVAs) to investigate post-intervention group differences). As the standardised assessments of WM, language and attention will be repeated within a short time-frame, results from the education as usual group will be used to examine test-retest effects. Qualitative analysis of the data gathered in the semi-structured interviews will be carried out using Braun and Clarke’s (2006) thematic analysis [95].

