**Methods:**

This is a three-arm, cluster randomised feasibility trial comparing RECALL to an existing programme (active control), and no-intervention (education as usual). We will recruit six schools in socially disadvantaged areas in one region of the UK. Two schools will be randomly allocated to each arm of the trial. In each school, one class of children (ages 4-5 years) of approx. 30 children will be involved in this study. Ten children in each class will be sampled purposefully for outcome measurement including: standardised assessments of WM, language and attention skills; teacher ratings of attention; and parent ratings of functional communication skills. These will be administered at baseline and 1-week post-intervention in order to test the acceptability of the measures. A process evaluation using semi-structured interviews with participants will explore the acceptability of RECALL and the procedures employed in this trial.

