## Methods/design

This study is a three-arm, cluster randomised feasibility trial with a parallel group design. The novel RECALL classroom programme will be compared to an existing intervention (ALP, the active control) and education as usual (the no intervention control). The delivery of the interventions at the classroom level necessitates the use of a cluster design for this study [34, 35] with each school constituting a cluster. The experimental RECALL programme and the active control intervention will be delivered by health professionals from the multi-disciplinary RISE teams once per week. Thus, they will demonstrate the programmes for the teachers who will then provide two further practice sessions during the week.

Children’s outcomes will be measured at two time points (baseline and 1-week post-intervention). The protocol has been developed according to the SPIRIT 2013 Statement [36] recommendations for protocol items for clinical trials and the CONSORT 2010 extension to cluster randomised pilot and feasibility trials [37]. Throughout the trial, a process evaluation will explore the factors that could impact on the internal and external validity of a future CRT and the intervention’s logic model for RECALL will be refined [38, 39]. Figure 1 shows the flow chart of the study and Fig. 2 illustrates the timing of all trial processes.

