### Randomisation and allocation

The six schools will be randomised to each arm of the trial: two will receive RECALL; two will receive the active control intervention (ALP); and two will receive education as usual. This will be conducted by the schools’ names being placed in opaque, sealed envelopes which will be selected by an independent person from within the lead researchers’ institute. This process has been deemed as introducing a low risk of bias in allocation concealment [51]. Randomisation will occur after baseline data collection with the children. As previously indicated, children will be selected for outcome measurement using stratification. The teacher will sort the names of all those whose parents provide written informed consent into the three strata previously specified. If more than the required number in each sub-group consent, the participants will be randomly selected using the same process of placing names in opaque envelopes.

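### Baseline ANOVAs by arm test differences that can only be chance, and treat 60 children as the randomised units when six schools are

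*Protocol article*

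**What the plan says.** The Data analysis section states that "between group comparisons will be conducted to inform the statistical model for the future trial". The first of two elements is "a series of one-way analyses (ANOVAs) of the baseline data" on the AWMA, the NEPSY subtests and a language measure, "to investigate pre-intervention group differences". The second is a set of ANCOVAs of post-intervention scores. The same section rules out one kind of testing: "statistical significance of treatment effects will not be analysed as this study would be under-powered for this purpose". That sentence covers treatment effects and does not mention baseline.

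On design, Methods/design describes cluster randomisation "with each school constituting a cluster". The abstract's Methods paragraph says "Two schools will be randomly allocated to each arm of the trial". Randomisation and allocation fixes the order of events: "Randomisation will occur after baseline data collection with the children". Stratification of children sets ten measured children per class, in fixed numbers of 5, 2 and 3 from three ability-related strata.

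**The concern.** There are two separate faults.

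- **The null hypothesis is already known to be true.** The children are consented, selected and tested before their school is drawn. Allocation cannot have affected a baseline score or who was measured. A p-value for an arm difference then tests whether random allocation was random. It does not show whether an imbalance matters or whether a variable predicts outcome.
- **The named test uses the wrong unit.** A one-way ANOVA by arm has no school term. It compares arms against variation between children, although chance differences between arms arise from drawing two schools for each.

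At stake is the reading of the feasibility results. A nominally significant baseline difference may be reported as a finding and carried into the definitive trial's model, which is the stated purpose of the comparison. The restriction on significance testing does not cover it. Nor does the statement under Sample size and participants that results will not be used for sample size, intra-cluster correlation or treatment effects.

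**Working it through.** **The plan's own figure.** 5 + 2 + 3 = 10 children per class, and 6 schools × 10 = 60, which matches the stated total. Each arm has 2 × 10 = 20. The protocol states no alpha, ICC or power, so there is nothing else to reproduce.

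**Inputs from the protocol.** 3 arms, 2 schools per arm, 10 children per school, strata 5/2/3 in every class. AWMA: 6 subtests (2 trained, 4 near-transfer).

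**Assumptions.**
- Alpha 0.05, normal scores, ICC from 0 to 0.20.
- Ten scores: 6 AWMA, 2 language scales and at least 2 NEPSY subtests. The NEPSY count is taken from the plural. The two language scales come from the NRDLS described under Data collection, although Data analysis names the CELF-P.
- Correlation 0.4 between scores.
- The concern and diagnosed strata lie 0.5 and 1.0 SD below the typically developing stratum, or 1.0 and 1.5 SD below.

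**Degrees of freedom.** The one-way ANOVA uses 2 and 60 − 3 = 57 df, critical F 3.16. An analysis of the six school means has 2 and 6 − 3 = 3 df, critical F 9.55.

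**Effect of schools.** With total variance 1 within strata, the between-arm mean square has expectation 1 + (10 − 1) × ICC. This is 1, 1.45, 1.90 and 2.80 at ICC 0, 0.05, 0.10 and 0.20. The error mean square does not rise with it.

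**Effect of the fixed strata.** Every class has the same mix, so stratum differences cancel between arms but remain in the error term.
- Gaps 0.5/1.0: stratum mean −(5 × 0.5 + 2 × 1.0)/10 = −0.45; variance (5 × 0.05² + 2 × 0.55² + 3 × 0.45²)/10 = 0.1225. This adds 60 × 0.1225/57 = 0.129 to the error mean square.
- Gaps 1.0/1.5: mean −0.80; variance (5 × 0.20² + 2 × 0.70² + 3 × 0.80²)/10 = 0.31. This adds 60 × 0.31/57 = 0.326.

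At ICC 0 the exact rejection rate is P(F(2,57) > 3.16 × 1.129) = 0.035 for the smaller gaps and P(F(2,57) > 3.16 × 1.326) = 0.020 for the larger. Both are below the nominal 0.05.

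**Simulated rates with no true arm difference** (good to about one percentage point):

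| ICC | Per test, with strata | Per test, strata ignored | At least one of 10, with strata | At least one of 10, strata ignored |
|---|---|---|---|---|
| 0 | 2-4% | 5% | 16-25% | 33% |
| 0.05 | 7-10% | 13% | 40-54% | 65% |
| 0.10 | 13-18% | 21% | 64-74% | 83% |
| 0.20 | 26-32% | 37% | 88-94% | 97% |

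At ICC 0.01 to 0.02, the chance of at least one with strata is 20-37%. With eight scores (no NEPSY) it is 12-20%, 36-48%, 58-70% and 84-91% at the four ICCs in the table.

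**What the alternatives do.** An ANOVA of the six school means returns the per-test rate to about 5% at every ICC tried, but with 3 error df it has negligible power. Description without a test has no error rate to control.

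**The case against.** The strongest case against is that this is an ancillary analysis in a feasibility study that makes no efficacy claim, and most of that stands. Criteria for proceeding to a full CRT rests progression mainly on recruitment, retention and completion of measures. The article gives no alpha or decision rule for the ANOVAs, so the harm arises only if they are read as tests. The fixed strata make the test conservative when the ICC is near zero, and the protocol gives no ICC. An analysis plan that is not shown might add a term for school, but the method named here is explicitly one-way.

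A reader might infer more than the text supports:

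- *Covariates for the definitive trial will be selected on noise.* The protocol says the comparisons inform the model but states no selection rule, and the ANCOVAs do not depend on the ANOVA results.
- *The results would distort the judgement of randomisation or of the comparator.* Table 3 assesses randomisation by consent rates, reasons given and teachers' views. It assesses the active control by health professionals' views and observed delivery. Neither uses baseline scores.
- *A spurious difference is close to certain.* Rates such as 83% or 97% ignore the strata and need an ICC of 0.10 or 0.20.
- *This protocol should name the sampling stratum as a covariate of the future model.* The strata serve to try out the measures here, and nothing says a later trial will sample in the same way.

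The feasibility label does not justify the test itself. An ANOVA is a significance test, none of the listed objectives calls for it, and its only stated use is to inform a later model.

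**Conclusion.** The point holds. Testing baseline by arm is uninformative because randomisation follows measurement; this needs no assumption. The one-way form also ignores the randomised unit. How much that matters depends on an ICC the protocol does not give. With the strata included, the per-test error is at or below nominal at ICC 0, modestly raised at 0.05, and about 13-18% at 0.10. At least one spurious difference is roughly even or less likely at ICC 0.05, and more likely than not from 0.10 upward in every scenario tried. These figures also rest on the assumed alpha, number of scores, correlation and stratum gaps. Severity is low to moderate: the analysis could mislead the design of the definitive trial, but it does not undermine the feasibility objectives or the progression decision.

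**What to change.** In Data analysis, delete element (1). Replace it with a descriptive table of baseline n, mean and SD for each score, by arm and by school, without tests. Add a sentence saying that observed baseline differences will not be used to choose covariates for the definitive trial, and that these will be chosen on prognostic grounds, such as the baseline value of the outcome. The change removes an analysis, needs no extra data and costs nothing beyond the edit.
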